All pre-operative measurements are part of standard care in the Netherlands and Belgium. Pre-operatively patients receive an audiometric exam, a physical examination of the ear, a CT-scan and fill in the patient-reported outcome measure (PROM). Follow-up will be planned at least at 6-18 weeks, at around 1 year and at around 3 years after surgery. It is important to note that conducting a CT scan and audiometry preoperatively as well as the DW-MRI's after 1 and 3 years are part of the standard care. In line with standard care, if there is a suspicion for recurrent or residual pathology (either clinically by micro-otoscopy or radiologically by DW-MRI) the treating physician will perform a revision surgery. If during revision surgery the suspicion is confirmed, the type of recidivism (residual or recurrent) is recorded and the follow-up of the patient ends. Data that is collected up until the point of detection of residual or recurrent disease will be used for analysis (this is not an exclusion criterium). If the suspicion is not confirmed (false-positive) then the patient will continue the follow-up as planned (unless a reconstructive procedure with the goal of improving hearing has been performed). During the three years of follow-up, patients should not undergo another type of ear surgery. If this is unavoidable, as judged by the treating physicians, the patient will be retrospectively excluded. In order to ensure that the same surgical data is collected in all participating centers, a standardized operation report will be written and shared by the sponsor (UMC Utrecht). This operation report will be recorded in the electronic patient dossier (with the exception of the information if obliteration was used or not) and transferred to Castor EDC. In Castor there will be a variable to also record if obliteration has taken place or not. The only methodology that is different to standard care is the randomization of the patients and the completion of the questionnaire. It is important to note that the technique used for the obliteration technique differs slightly between centers. The exact surgical technique will be described by the participating otologists and included in the description of the study, for example in a publication.

**Figure 1.** Flowchart of the study. *Standard care is indicated by \**[figure not shown]

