#### 6.1.2 Secondary study parameters/endpoints

- **Baseline characteristics:**
  - Patient demographics (age (as collected by birthyear), gender), date of first presentation at the outpatient clinic, date of surgery, operated side (right/left), applied antibiotic treatment within in 2 weeks prior to surgery.
  - Co-morbidities and lifestyle factors: smoking, obesity, asthma, diabetes, COPD, allergies, rhinosinusitis.
  - Amount and type of all previous ear surgeries which are not mentioned in the exclusion criteria.
- **Hearing outcome:**
  - As measured by audiometric testing (pure-tone average thresholds (PTA) as calculated over 0.5, 1, 2 and 4 kHz for the air-conduction (AC) and bone-conduction (BC) and speech audiometry. This will be measured before the surgery, and at 6-18 weeks and around 1 year after surgery. The pre-operative audiogram should not have been measured more than 6 months prior to surgery.

- **Surgical characteristics:**

- A short 'standard' surgical report/template written by the participating otologists per center will be collected and used in the scientific publication to demonstrate any potential differences in surgical technique. This **does not** include patient information.
- STAMCO-classification: Localization and extension of the cholesteatoma, presence of preoperative complication status and the ossicular chain status before/at the time of removal of the cholesteatoma will be recorded. Any differences in outcomes in STAMCO classifications between the two randomized groups will be evaluated and described.

**Figure 2:** Localization, disease extension and complications as described by the STAMCO classification (18, ten Tije et al.)

[figure not shown]

- Material used for obliteration (Bonalive®, bonedust, hydroxyapatite, cartilage, muscle) as registered in the surgical report.

- Ossicular chain reconstruction (OCR); performed (yes/no), if yes, the used material and type of reconstruction (PORP, TORP, use of incus interposition, type 3 tympanoplasty) will also be reported.
- Surgical personnel: It is registered if an ENT-doctor in training (resident) or fellow has operated along with the specialist.
- Surgical time: Surgery time is recorded in minutes for each surgery and described.
- Revision surgery during follow-up: the information and observations as gathered by the surgical report will be collected from all revision surgeries performed during the follow-up of this study.
- **Complications**

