  - Caused by the cholesteatoma (e.g. labyrinth fistula, dura defect, meningoencephalocele, dehiscence of facial nerve, interrupted bony tegmen plate, etc.).
  - Complications during or after surgery (e.g. wound infection, bleeding, damage to the inner ear (resulting in perceptive hearing loss or dizziness), damage to the facial nerve causing facial paralysis, damage to the taste nerve resulting in change in taste, intracranial complications (damage to the tegmen, liquor leakage), tinnitus).
  - Complications that occur within the first 6 weeks after surgery will be registered
- **Quality of life:** Is quality of life comparable between the two techniques? This will be measured using a validated patient reported outcome measure (PROM) in the form of an otological questionnaire (OQUA) and two generic quality of life questionnaires before and after the surgery (27).
  - **OQUA:** This is a otological questionnaire and includes 34 questions, covering eight major types of ear complaints (earache, pressure in the ear, hearing loss, tinnitus, otorrhoea, itch, dizziness, and loss of taste). It measures the frequency and severity of these ear complaints and the impact on quality of life.
  - **EQ5D-5L and HUI3:** The utility scores will be measured to be able to conduct an economic evaluation as described below.
- **Economic evaluation:** A cost-utility analysis will be performed according to the Dutch guideline for economic evaluations in healthcare. Differences with the Belgian guideline for economic evaluations, such the perspective, will be accounted for in the scenario analyses. For instance, in the base case, we will perform the analysis using a societal perspective. In the scenario analysis, we will include a healthcare perspective based on the Dutch base case analysis,

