## 7.2 AEs, SAEs and SUSARs

### 7.2.1 Adverse events (AEs)

Adverse events are defined as an undesirable experience occurring to a subject during the study. Adverse events that will be reported are the following: Complications during or after surgery (e.g. wound infection, post-operative bleeding, damage to the taste nerve resulting in change in taste, tinnitus). These are the same complications that are also mentioned by the treating physician in standard clinical care and for which informed consent is asked when discussing the surgical operation. From professional experience we will report complications that occur within the first 6 weeks after surgery. We consider this to be a relevant period in which complications due to the intervention can occur.

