### 7.2.2 Serious adverse events (SAEs)

A serious adverse event is any untoward medical occurrence or effect that

- results in death;
- is life threatening (at the time of the event);
- requires hospitalisation or prolongation of existing inpatients' hospitalisation;
- results in persistent or significant disability or incapacity; or
- any other important medical event that did not result in any of the outcomes listed above due to medical or surgical intervention but could have been based upon appropriate judgement by the investigator.

An elective hospital admission will **not** be considered as a serious adverse event.

**This study is expected to pose a negligible risk for patients; any SAEs occurring during the study period are expected to be related to the standard treatment and not to the study intervention.** SAE's which could occur as a result of the operation and are always discussed with the patient beforehand as part of standard care are: damage to the inner ear (resulting in perceptive hearing loss or dizziness), damage to the facial nerve causing facial paralysis, intracranial complications. These will only be reported if they occur during or within the first six weeks after surgery as a later onset cannot be seen as a consequence of the intervention.

The investigator will report all SAEs to the sponsor without undue delay after obtaining knowledge of the events. The investigator reports this to the principal investigator and coordinating investigator of the sponsor (UMC Utrecht) per secured e-mail. The sponsor

will report the SAEs through the web portal *ToetsingOnline* to the accredited METC that approved the protocol, within 7 days of first knowledge for SAEs that result in death or are life threatening followed by a period of maximum of 8 days to complete the initial preliminary report. All other SAEs will be reported within a period of maximum 15 days after the sponsor has first knowledge of the serious adverse events.

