### **7.3 Follow-up of adverse events**

From professional experience we will report complications that occur within the first 6 weeks after surgery. We consider this to be a relevant period in which complications due to the intervention can occur. All AEs will be followed until they have abated, or until a stable situation has been reached. Depending on the event, follow up may require additional tests or medical procedures as indicated, and/or referral to the general physician or a medical specialist. SAEs need to be reported till end of study within the Netherlands, as defined in the protocol.

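### Complications count only if they arise within 6 weeks of surgery, yet no assessment is scheduled in that window and no rule dates deficits first found at the 6-18 week visit

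*Protocol*

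**What the plan says.** The complication endpoint in section 6.1.2 covers events during or after surgery. Its examples include wound infection, bleeding, facial nerve damage, taste change, tinnitus and "damage to the inner ear (resulting in perceptive hearing loss or dizziness". The time limit is: "Complications that occur within the first 6 weeks after surgery will be registered".

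The safety sections use the same limit:

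- Section 7.2.1 (AEs), repeated in 7.3: "From professional experience we will report complications that occur within the first 6 weeks after surgery".
- Section 7.2.2 (SAEs), on inner-ear, facial nerve and intracranial damage: "These will only be reported if they occur during or within the first six weeks after surgery". The reason given is that "a later onset cannot be seen as a consequence of the intervention".
- Section 7.3 then adds: "SAEs need to be reported till end of study within the Netherlands, as defined in the protocol".

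On the schedule, section 3 says "Follow-up will be planned at least at 6-18 weeks, at around 1 year and at around 3 years after surgery". For audiometry, section 6.1.2 says "This will be measured before the surgery, and at 6-18 weeks and around 1 year after surgery". Table 1 in section 6.3 agrees: after surgery on day 0, the next column is 6-18 weeks, with the visit and micro-otoscopy, audiometry and the first postoperative OQUA.

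**The concern.** The rule depends on when a complication began, but the protocol plans no observation before the date on which the rule expires. A complication that shows itself, or that the patient brings to the clinic, can be dated. One that is recognised only by audiometry or by asking may first come to light at a visit up to 18 weeks after surgery, and the protocol does not say how it is then dated or attributed.

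The endpoint could therefore be applied differently between centres, and between early and late visits within a centre. The decision would fall to surgeons who, by sections 3 and 6.2, know the allocation. It also matters outside the publication: section 6.7 ties possible early termination to SAEs occurring more often than expected, section 7.2.2 names inner-ear damage as a possible SAE, and section 8.3 plans no interim analysis.

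**Working it through.** The plan gives no computed figure on this point, so the check compares its dates and definitions.

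**1. Overlap of the two windows**

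- Registration window: 6 weeks × 7 = day 42, so day 0 to day 42 (sections 6.1.2, 7.2.1, 7.2.2, 7.3).
- First visit, audiogram and OQUA: 6 × 7 = day 42 to 18 × 7 = day 126 (sections 3 and 6.1.2, Table 1).
- Possible visit days: 126 − 42 + 1 = 85. Days shared with the registration window: 1 (day 42).
- Longest lag from the limit to the first scheduled look: 18 − 6 = 12 weeks.

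**2. What a late audiogram can date**

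A threshold shift first measured at week t arose at some time between the preoperative audiogram and week t. For t = 12, the first 6 postoperative weeks lie inside the limit and the next 6 outside. For t = 18, the split is 6 and 12. The measurement cannot tell these apart. The preoperative audiogram may itself be up to 6 months old at surgery (section 6.1.2), which widens the interval further.

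**3. Which listed complications this touches**

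- Little or not at all: bleeding, facial paralysis, liquor leakage and many wound infections. These are seen at surgery or make the patient present.
- Exposed: perceptive hearing loss, which needs bone-conduction audiometry. Also taste change, tinnitus and milder dizziness, which may go unrecorded until someone asks.

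**4. Whether another planned analysis fills the gap**

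- Hearing: the only derivation named in section 8.2 is the air-bone gap, which is AC − BC. If a perceptive loss raises both thresholds by d, then (AC + d) − (BC + d) = AC − BC. The gap does not change, so this measure does not show a pure inner-ear loss.
- OQUA: it covers taste, tinnitus and dizziness and is completed at 6-18 weeks, but the model in section 8.2 uses 12 and 36 months only.
- Bone-conduction averages are collected before surgery and at 6-18 weeks in both arms, but nothing links them to the complication endpoint.

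**5. SAE period**

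Section 7.2.2 restricts reporting of the named surgical SAEs to six weeks. Section 7.3 says SAEs are reported until the end of the study within the Netherlands. For the same event these give different instructions.

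**The case against.** The strongest reply is that the limit is on occurrence, not detection. Section 7.2.2 justifies it by onset, and no section requires a complication to be found within 6 weeks. Inner-ear damage from surgery would be expected to arise at or soon after the operation, so a loss found at week 12 can still be registered. This stands: late assessment does not by itself exclude an event. It does not supply the missing rule for deciding when onset is unknown.

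Second, the listed visits are a minimum, procedures run through standard care, and clinical data come from the health record (sections 3 and 6.3). Earlier contacts are therefore possible, and a visit exactly at week 6 meets the limit. This also stands in part. However, no earlier contact is named, and Table 1 marks the 6-18 week visit itself as standard care.

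Third, the raw data are not lost: bone-conduction thresholds are measured in both arms, and blinded patients complete the OQUA. This is true, and it makes the repair cheap. A SAP that is not shown could define a bone-conduction derivation, but it could not recover onset dates or findings that the CRF did not ask for.

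Three stronger readings are tempting, and the documents do not support them:

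- That all surgical complications are assessed only after the window closes. Acute complications are not.
- That harm in the obliteration arm would be hidden. The hearing risk in section 1 comes from removing part of the ossicular chain, which is a different mechanism from inner-ear damage, and hearing has its own endpoint. The same registration rule applies to both arms.
- That complication rates are understated by a known amount. The protocol gives no incidence from which to calculate one.

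**Conclusion.** The point holds in a limited form. No assessment is scheduled inside the 6-week window apart from a visit that happens to fall on its last day, and the first one may come up to 12 weeks after it. For complications that need a test or systematic questioning, registration then turns on an onset date that the schedule may not supply, and no rule covers that case. The number of affected patients and any effect on the comparison between arms cannot be estimated from the protocol.

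This rests on two assumptions: that complications are registered by the treating surgical team, which the text implies but does not state, and that routine care does not systematically test or question patients before week 6. If every centre did so, the gap would be small.

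Separately, the contradiction between sections 7.2.2 and 7.3 on the SAE reporting period stands whatever is decided about the endpoint. It is worth correcting because the remedy uses data already collected.

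**What to change.** 1. In section 6.1.2, register listed complications first found at the 6-18 week visit as well as those seen earlier. Record the onset date where known, and mark it unknown otherwise, so that the 6-week count can still be shown beside the wider one.
2. Derive inner-ear damage in both arms from the change in bone-conduction pure-tone average between the preoperative and 6-18 week audiograms. Use one threshold, fixed before any comparison by arm. The protocol gives no basis for a particular value, so the sponsor must choose and justify it.
3. Align sections 7.2.1, 7.2.2 and 7.3 with the revised registration rule. Section 7.2.2 must be included, because that is where inner-ear damage is named as an SAE.
4. Reconcile the six-week limit in section 7.2.2 with the end-of-study reporting period in section 7.3.

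The cost is protocol and CRF wording, with no added visit or test. The bone-conduction measure can also be derived for patients already operated on, since it uses audiograms the protocol already requires. The downside is that reported complication rates will be somewhat higher and may include a few events unrelated to surgery, including threshold shifts that arose between an older preoperative audiogram and the operation.

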as well as a scenario analysis using healthcare perspective and Belgian unit costs and QoL value set. The cost-utility analysis will be performed with a lifetime time horizon. Data will be collected alongside the clinical trial and extrapolated over lifetime using a decision-analytical model. Unit costs of both procedures and of reinterventions will be calculated with a bottom-up approach using duration of surgery, personnel, disposables and materials used. Other healthcare resource use, for instance admissions, out-patient consultations, GP visits and paramedic care, will be collected using patient-reported healthcare resource use using the Institute for Medical Technology Assessment Medical Consumption Questionnaire (iMCQ). Productivity losses will be collected with the Institute for Medical Technology Assessment Productivity Cost Questionnaire (iPCQ). Both questionnaires will be adjusted for the patient population and the Belgian setting together with clinical experts and patient input. Healthcare resource use will be multiplied with unit costs from the Dutch costing manual and Belgian unit costs in a scenario analysis. The PIF is adjusted to enable validating healthcare resource use later on if necessary with claim data, such as in the IMA data linkage or VEKTIS data. For Belgian participants, the national number (RRN/INS) will be collected to enable possible data linkage with billing data from RIZIV/INAMI for validation purposes. If deemed necessary based on the trial results, approval will be requested from the competent chamber of the Information Security Committee to have the relevant study data linked with IMA data by a trusted third party (TTP, eHealth platform) using the patient national number. The national number will not be included in the trial database. This data linkage will be performed to obtain a more complete data set containing costs related to health care paid by the compulsory health insurance and the patient. This linked information will be used for the analysis of effectiveness and cost-effectiveness of the intervention.

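### The request to link Belgian claims data depends on the trial results, and the protocol contradicts itself on whether linked costs only check the cost-effectiveness analysis or enter it

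*Protocol*

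**What the plan says.** All of this is in Protocol 6.1.2, under the economic evaluation.

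- **Planned cost sources.** Procedures and reinterventions are costed bottom-up. Other healthcare use comes from the patient-reported iMCQ, and productivity losses from the iPCQ. On pricing: "Healthcare resource use will be multiplied with unit costs from the Dutch costing manual and Belgian unit costs in a scenario analysis". On perspective: "in the base case, we will perform the analysis using a societal perspective".
- **Claims data, first mention.** "The PIF is adjusted to enable validating healthcare resource use later on if necessary with claim data, such as in the IMA data linkage or" (the sentence then names VEKTIS as the alternative).
- **Claims data, second mention.** The national number of Belgian participants is collected "to enable possible data linkage with billing data from RIZIV/INAMI for validation purposes".
- **Trigger.** "If deemed necessary based on the trial results, approval will be requested from the competent chamber of the Information Security Committee".
- **Purpose.** "This data linkage will be performed to obtain a more complete data set containing costs related to health care paid by the compulsory health insurance", together with costs borne by the patient.
- **Use.** "This linked information will be used for the analysis of effectiveness and cost-effectiveness of the intervention".

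The economic evaluation entry in section 8.2 only refers back to the methods section.

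**The concern.** There are two problems, and each makes the other worse.

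First, the trigger is tied to the results and is not restricted to anything independent of treatment arm. Nothing written prevents the team from looking at the incremental cost or the cost-utility result and only then deciding whether to bring in another source.

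Second, the role of that source is not settled. If linked data only check the questionnaire, a late decision to link does little harm to the estimate. If they feed the cost-effectiveness analysis, the same late decision becomes a choice of input made with the answer in view: an unwelcome result can be re-examined with new data and a welcome one left alone.

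At stake is the credibility of the cost-utility result and of the budget impact estimate built on it. A payer shown a result that includes linked costs could not tell whether linkage would also have been sought had the first result pointed the other way.

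**Working it through.** The protocol gives no figure on this point, so there is none to reproduce. The check is a reading of the relevant text side by side.

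**Step 1: is the trigger limited anywhere?**

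| Place in protocol | What it contributes |
|---|---|
| 6.1.2, trigger sentence | Necessity is judged on the trial results; no criterion, decision-maker or blinding condition |
| 6.1.2, last paragraph of the economic evaluation | Lists deterministic, probabilistic, scenario and value-of-information analyses; linked data are not placed in any of them |
| 6.2 | Only participants are blinded |
| 8.2, economic evaluation | Refers back to the methods; no rule on cost source |
| 8.2, missing data | Multiple imputation; does not say how this relates to linkage sought for completeness |

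No other section confines the trigger to something that cannot reveal the between-arm difference.

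**Step 2: what role do the linked data have?**

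| Statement in 6.1.2 | Role implied |
|---|---|
| Participant information adjusted for later use of claims data | Validation of resource use |
| National number collected for Belgian participants | Validation |
| Purpose of the linkage | Fuller cost data, which goes beyond validation |
| Final sentence on linked information | Input to effectiveness and cost-effectiveness analyses |

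The first two and the last cannot all describe the same use. The text does not say whether linked costs would replace, supplement or only check the iMCQ costs.

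**Step 3: which parts of the analysis are exposed?**

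| Component | Planned source | Could linkage as described touch it? |
|---|---|---|
| Surgery and reinterventions | Bottom-up costing | Not stated; the planned method does not depend on claims |
| Other healthcare use | iMCQ | Yes; this is the main overlap with care paid by the insurer and the patient |
| Productivity losses | iPCQ | No; outside the costs the linkage is said to cover |
| Recidivism (6.1.1, 8.1) | Micro-otoscopy, DW-MRI, findings at revision surgery | Section 8.1 makes no use of linked data |

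The approval route is described only for Belgian participants. For Dutch participants VEKTIS appears only as an optional check. The protocol does not give the number of Belgian participants, so the affected share of the trial cannot be calculated. If linked costs did enter the analysis, the source of healthcare costs could differ by country.

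**Step 4: what follows?** A results-dependent trigger (step 1) combined with permission to use the data in the analysis (step 2) leaves a route by which one cost component, in one part of the sample, could change after the incremental result is known (step 3).

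**The case against.** The strongest reply is that the phrase about trial results may mean no more than the completeness or plausibility of the questionnaire data. The sentences before it concern validation, and the one that gives the purpose concerns completeness. That reading is reasonable and may be what was intended. It is not what is written, and if it is the intent, one clause settles the matter.

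A second reply is that the cost sources are already fixed. This largely stands. A reader might infer that the team is free to choose its cost source at the end, or that billing data would replace the questionnaires, so that no pre-planned result would exist. The documents do not support this: bottom-up costing, the iMCQ, the iPCQ and Dutch unit costs are named, nothing says that linked data replace them, and an analysis on those sources can be identified and reported.

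A third reply is that detail on base case and scenarios belongs in an analysis plan that is not shown here. That is fair for the detail. It does not dispose of the two statements in the protocol itself, the trigger and the contradictory role, which would still need correcting.

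A reader might also want to express the problem as an inflated false-positive rate. Two correlated tests of a null cost difference, with freedom to rely on either, would give at least one p<0.05 in about 7% of trials at a correlation of 0.9 and about 9% at 0.5, instead of 5%. These figures are purely illustrative. The correlations are assumed, and the plan is a lifetime decision model with sensitivity analyses; section 8 sets a general 0.05 threshold but names no test of incremental cost. They are not the size of this finding.

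Finally, the word effectiveness might suggest that the primary comparison is open to the same choice. Section 8.1 does not mention linked data, and the endpoint is clinical, radiological and surgical.

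**Conclusion.** The concern holds in a limited form. The protocol makes the linkage request depend on the trial results without requiring independence from the between-arm comparison, and it contradicts itself on what the linked data are for. A supplementary cost source could therefore enter a secondary analysis after its result is known.

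The size is bounded in kind rather than in number: mainly iMCQ-type healthcare costs, in detail only for Belgian participants, in the cost-effectiveness and budget impact results. The planned analysis on the named sources and the primary recidivism comparison are not undermined. The conclusion rests on the protocol text alone. A separate economic analysis plan might settle the role of the linked data, but the trigger as worded in the protocol would still need to change. It should be corrected, because correction is cheap now and independence from the results cannot be demonstrated later.

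**What to change.** Amend Protocol 6.1.2 and carry the same wording into the economic analysis plan.

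1. **Trigger.** Replace the dependence on trial results with a rule judged blind to arm, for example pooled iMCQ completeness or plausibility, decided and recorded before any cost is compared by arm. Alternatively, commit in advance to linkage for all participants who consent to it.
2. **Role.** State that the sources already named (bottom-up costing, iMCQ, iPCQ, Dutch unit costs) form the base case, and that linked costs are a validation or a named scenario analysis restricted to the linked participants.
3. **Last sentence on linked information.** Bring it into line with the validation statements. Delete the reference to effectiveness, or say which outcome the billing data would supply.

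The cost is a few sentences of text. The one practical drawback is that the request to the Information Security Committee may have to be filed earlier, possibly for a linkage that turns out not to be needed.
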